##### Analysis

The analysis plan is similar as for hypothesis 1. We will use GEE to estimate odds of adhering to CPAP treatment at 6 and 12 months. This aim does not require any changes or additions to our procedures.

##### Tertiary aim

To determine which individual- and contextual-level factors affect the relationship between peer health education and OSA evaluation and treatment. We hypothesize that individual-level factors (OSA knowledge, OSA self-efficacy, and past evaluation behavior) and contextual level factors (i.e., noise levels, room temperature, neighborhood factors, trust/rapport with peer educators, family network, and socioeconomic position) will mediate effects of peer education on adherence to OSA evaluation and recommended treatment.

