### Phase III: OSA assessment and diagnosis – home study and sleep clinic assessments and treatment customization

#### Primary trial outcome: sleep home study

The research staff will conduct an 8-day home study to collect sleep data via actigraphy (ActiGraph WGT3X-BT monitor) and a daily sleep diary, as well as environmental influences of sleep, such as noise and temperature, two factors that may confound sleep duration and quality. On day 1 of home sleep, a study technician will visit the participant’s home to place the ActiGraph watch on the participant’s wrist as well as connect a sound device and thermometer to capture the participant’s physical sleep environment. During the visit at the participant’s home, staff will demonstrate how the WatchPAT™ home sleep test device is used, worn on the wrist and fingertip on the last night of a 7-day sleep diary. On the seventh day of the home evaluation, the study’s technician will re-visit the participant’s home to set-up a device, the WatchPAT™ portable sleep test device to determine the severity of OSA risk. The WatchPAT™ is an in-home device utilized for OSA evaluation cleared by the Food and Drug Administration and approved by the Center for Medicare & Medicaid Services [93, 94]. It measures blood oxygen saturation, pulse rate, airflow, respiratory effort (a combined signal using pressure transducer sensing forehead venous pressure, venous volume by photoplethysmography), and snoring levels. Automated analysis of physiologic data yields OSA indices that reflect OSA risk, which is verified by a trained human scorer to ensure accuracy of signal interpretation. The device integrates physiologic, clinical, and anthropomorphic data to determine the presence and severity of OSA. Correlation between the WatchPAT 200 and PSG recordings was 0.96 using AHI with a 4% desaturation. Diagnostic sensitivity and specificity of in-home WatchPAT using AHI ≥ 15 (in the absence of OSA symptoms) are 0.85 and 0.91, respectively [93]. Based on Medicare guidelines [95], those with an AHI ≥ 10 will be referred for treatment (American Academy of Sleep Medicine guidelines) [96]. We chose this criterion to ensure that we reduce the rate of false negative results. In the 7-day sleep diary, participants will indicate (1) nap time and duration, (2) medications/drugs promoting night-time sleep or daytime alertness (e.g., caffeine), (3) time to bed, (4) time of lights off, (5) final time of awakening, (6) final time of arising, and estimated (7) sleep latency, (8) sleep duration, (9) wake after sleep onset, (10) sleep quality, and (11) daytime sleepiness. On day 8, the study staff will retrieve all devices and data from the sleep diary.

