#### Sample size and power analysis

We plan to screen approximately 1250 blacks in the community. Assuming 39% of blacks are at risk for OSA, we propose to enroll 398 men and women (199 per study arm). With a 35% attrition rate, 258 will have provided adherence data during 6-month follow-up assessment. Based on the pilot data, we expect that 41% in the intervention arm (*n* = 82) and 26% in the attention-control arm (*n* = 52) will have completed all aspects of the trial, including site interview, home evaluation, and follow-up assessment (Fig. 2).

The primary study outcome is receipt of home OSA evaluation after tailored peer-based sleep health education. Data obtained from a sample of blacks provided a current estimate of the likely OSA evaluation rate we expect in the partner community. Analysis showed that 41% of participants adhered to recommended OSA evaluation after intervention exposure, whereas 26% of participants in a control group agreed to undergo evaluation. These preliminary findings represent the likely adherence rates expected in our proposed study.

We propose to achieve an evaluation rate in our intervention arm of 41% based our pilot study mentioned above. This would represent a 63% greater adherence rate compared with controls, which potentially would have a significant public health impact. Assuming a 15% increase in the likelihood of undergoing home-based OSA evaluation, a standard error of 0.09% and a sample size of 398, the study will be adequately powered (> 85%) to detect a significant increase in adherence. Specifically, an observed difference of 15% would be reported with a 95% CI 7–24%. A two-tailed test, with 80% power and α = 0.035 comparing adherence rates of 26% with 41% requires 199 participants per group. Of note, our sample size estimate adjusted for potential intra-cluster coefficient that may be observed in both the treatment and control arms, which according to our initial pilot was 0.014. The resulting effective sample size (*ESS = [M x K/DE]*) after adjustment for design effect (*DE*)… [*DE = 1 + (n-1)ρ*] was *n* = 398 (199 participants per arm) [97, 98]. The study is also powered to assess differences in adherence rates to CPAP treatment between the two arms considering the likely attrition rate of 35% during follow-up assessment.

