##### Analysis

We chose these individual and contextual factors based on research showing acceptable effect size in predicting adherence status (e.g., home-study adherence, sleep clinic adherence, and CPAP device adherence) [102]. We will examine the path toward adherence to OSA evaluation and CPAP treatment using structural equation modeling, which will determine influences of mediating/moderating factors on the role of peer education in improving adherence to OSA evaluation and treatment. Specifically, we will utilize moderated path analysis using the Baron and Kenny model [97, 98, 103]. Alternatively, we will explore whether causal mediation analysis might prove a better fit for our data than the Baron and Kenny model. Causal mediation analysis compared to structural equation modeling is a more flexible model, as it is based on a counterfactual framework and may be more appropriate for causal inference, especially in the presence of measured confounding [104, 105]. It should be noted that, if our statistical analysis plan changes, we will update this in the *Trials* journal.

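### The tertiary aim calls every listed factor a mediator, but noise and temperature cannot mediate home-study uptake, and past behaviour and baseline socioeconomic position cannot mediate at all

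*Protocol article*

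**What the plan says.** The section Tertiary aim hypothesises that a list of factors "will mediate effects of peer education on adherence to OSA evaluation and recommended treatment". The list has two parts: "individual-level factors (OSA knowledge, OSA self-efficacy, and past evaluation behavior", and contextual factors given as "noise levels, room temperature, neighborhood factors, trust/rapport with peer educators, family network, and socioeconomic position". That makes three plus six, or nine, all given the same role.

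Noise and temperature come from the home study. Under Primary trial outcome: sleep home study, a technician visits on day 1 to "connect a sound device and thermometer to capture the participant’s physical sleep environment". No other measurement of them is described. The same section gives them a different role: "such as noise and temperature, two factors that may confound sleep duration and quality".

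Uptake of the home study is the main endpoint. Sample size and power analysis states: "The primary study outcome is receipt of home OSA evaluation after tailored peer-based sleep health education". Study rationale codes it yes or no according to whether the person took part.

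On method, the Analysis subsection under Tertiary aim says: "Specifically, we will utilize moderated path analysis using the Baron and Kenny model". It then allows a counterfactual mediation analysis instead, if that proves to suit the data better. This subsection and the Discussion speak of mediators and moderators together, without saying which factor is which.

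**The concern.** A mediator of a randomised intervention must meet three conditions. It arises after randomisation and can be changed by the intervention. It comes before the outcome. It is observed both in people who have the outcome and in people who do not. The hypothesis applies the term to all nine factors, although the article's own account of how and when they arise shows that four do not meet these conditions for at least one of the named outcomes.

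If the hypothesis were followed as written, one part of the mechanism analysis could not be fitted, and another would report a quantity that randomisation sets to zero in expectation. Neither could support a statement about how peer education works.

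**Working it through.** **Inputs.** 199 per arm, 398 in total, with expected rates of 41% (n = 82) and 26% (n = 52), all from Sample size and power analysis. Those counts are given there for completing all parts of the trial including the home evaluation, and the same percentages serve there as the expected home-evaluation rates.

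**Step 1: reproduce the plan's counts.**
- Intervention: 199 × 0.41 = 81.6, rounded to 82.
- Control: 199 × 0.26 = 51.7, rounded to 52.
- Both agree with the article.

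**Step 2: noise and temperature on home-study uptake.**
- With recordings: 82 + 52 = 134, and 134 / 398 = 34%.
- Without recordings: 398 − 134 = 264, and 264 / 398 = 66%.
- An indirect effect needs a path from arm to mediator (a) and a path from mediator to outcome (b). Estimating b requires the outcome to vary among people whose mediator is observed.
- The devices are installed only once the home study has begun. Among those with a recording, the probability of uptake is therefore 1 and the outcome variance is 1 × (1 − 1) = 0, so b cannot be estimated.
- Imputation has nothing to draw on, because nobody who never began the study is observed.

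**Step 3: factors fixed before randomisation.**
- For a variable already determined at randomisation, the expected difference between arms is zero, so a = 0 in expectation and the indirect effect is zero by design.
- What remains is chance. For a standardised variable, the standard error of the arm difference is √(1/199 + 1/199) = √(2/199) = 0.10 SD, so differences of up to about 1.96 × 0.10 = 0.20 SD in either direction are within ordinary chance with no mediation at all.
- A simulation of 4,000 trials of 398 agrees: mean arm difference 0.001 SD, and a 5% test of arm on the variable rejects in 4.9% of trials.
- Past evaluation behaviour belongs here by its name. Socioeconomic position belongs here as measured at baseline: education, insurance and household income are background items under Sociodemographic variables.

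**Step 4: noise and temperature on the later outcomes.** Clinic attendance and CPAP use normally follow the home study, so the order in time is acceptable. The recordings still exist only in a subset formed after randomisation, expected to hold 41% of one arm and 26% of the other. The arms within that subset are no longer randomised groups.

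**The case against.** The strongest reply is that moderation is already planned. The opening sentence of the tertiary aim asks which factors alter the relation between education and outcome, which reads like moderation. The analysis text names moderated path analysis, and the Discussion names both roles. On this view the defect is one loose verb, and allocating factors to roles is ordinary detail for an analysis plan that is not shown. Part of this stands: the wording elsewhere softens the problem. It does not remove it, because the hypothesis itself says only that the factors mediate, applies that to every one of them, and nothing in the article moves any factor to the other role.

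A reader might infer several stronger points that the documents do not support:
- *Noise and temperature can mediate nothing.* Time order excludes them only for home-study uptake. They precede clinic attendance and CPAP use.
- *Every recorded participant must have outcome yes.* Primary aim and outcome defines adherence by successful completion. A few people could have devices installed on day 1 and not finish. That would add a few recordings with outcome no, but none for people who never began.
- *Knowledge and self-efficacy are measured too late.* The article does not say which wave enters the model, and a correctly ordered choice is available.
- *The Baron and Kenny approach would misstate the share mediated by some given amount.* No link function is stated for the mediation models. Any figure would depend on an assumed mediator strength and on the denominator chosen, so none is offered here.

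Socioeconomic items might also be asked again at follow-up, since the questionnaires are repeated. The article nevertheless describes no route by which peer education would change them.

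**Conclusion.** The point holds for four of the nine factors. For noise and temperature it is decisive on home-study uptake, where about 264 of 398 participants (66%) would have no value and the outcome is essentially constant in the rest. For past evaluation behaviour and baseline socioeconomic position, the arm-to-mediator path is zero in expectation, so any mediated effect reported would be chance imbalance.

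This rests on three assumptions: the plan's rates of 41% and 26% apply to home-study uptake; noise and temperature are recorded only as described; and past evaluation behaviour means behaviour before enrolment. The missing fraction moves with the rates, but the argument that the path cannot be estimated does not depend on them.

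Knowledge, self-efficacy and rapport remain plausible mediators. Neighbourhood factors and family network are not judged here. A reader might infer that the trial's main result is at risk. It is not: the aim is tertiary, and no sample size, power or primary estimate depends on it.

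**What to change.** In Tertiary aim:
- Keep as mediators only factors that arise after randomisation and that the intervention can change (OSA knowledge, self-efficacy, rapport), using values measured before the outcome in question.
- Treat past evaluation behaviour and socioeconomic position as baseline moderators, through an arm-by-factor interaction, or as covariates.
- Remove noise and temperature from the home-study pathway. Label any use of them for clinic attendance or CPAP adherence as exploratory and non-randomised, because it is confined to a subset selected after randomisation.

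In the Analysis subsection that follows, preferably make the counterfactual mediation approach, which the plan already names, the stated method for the yes/no adherence outcomes, instead of deciding on it by how well it suits the data.

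The change is to wording only and needs no new data. It has costs. Fewer factors are tested as mediators. Requiring the mediator before the outcome excludes events that occur before the follow-up measurement. A mediator taken at 6 months is also exposed to the 35% attrition that the plan expects by then.

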##### Analysis

We chose these individual and contextual factors based on research showing acceptable effect size in predicting adherence status (e.g., home-study adherence, sleep clinic adherence, and CPAP device adherence) [102]. We will examine the path toward adherence to OSA evaluation and CPAP treatment using structural equation modeling, which will determine influences of mediating/moderating factors on the role of peer education in improving adherence to OSA evaluation and treatment. Specifically, we will utilize moderated path analysis using the Baron and Kenny model [97, 98, 103]. Alternatively, we will explore whether causal mediation analysis might prove a better fit for our data than the Baron and Kenny model. Causal mediation analysis compared to structural equation modeling is a more flexible model, as it is based on a counterfactual framework and may be more appropriate for causal inference, especially in the presence of measured confounding [104, 105]. It should be noted that, if our statistical analysis plan changes, we will update this in the *Trials* journal.

#### Ancillary studies and post-trial methods

It is likely that participants from the current study may be eligible for related ancillary studies. In such cases, only participants who endorsed being contacted for future studies will be contacted about ancillary studies. The study team will determine whether involvement in an ancillary study will interfere with the current study. If the ancillary study will interfere, we will defer enrollment until the participant is finished with all study procedures of the parent study. It is also likely that participants may be contacted about future studies after participating in the study. We will only contact participants who requested to be contacted.

## Discussion

The current study is an outgrowth of our previous National Institute on Minority Health and Health Disparities-funded randomized controlled study (NCT01946659), which investigated whether blacks with metabolic syndrome are at increased risk for OSA. During the study, many black patients were unwilling to undergo a laboratory sleep evaluation to determine if they had diagnosable OSA. The proposed study will be the first randomized trial to utilize home-based sleep recordings to assess OSA risk among blacks. In addition, our study is innovative in the following ways.

To our knowledge, this will be the first culturally and linguistically tailored, community-engaged, peer-based sleep health intervention to increase adherence to OSA evaluation and treatment. Although peer education is not a novel concept [60, 106, 107], its effectiveness remains untested among blacks with OSA. Second, while peer education may be effective in increasing OSA assessment behavior, it may be insufficient to achieve optimal adherence to CPAP therapy since common side effects (e.g., mask fitting, pressure, nasal irritation, and claustrophobia) that negatively affect adherence are routinely addressed at the clinic. Thus, individuals showing poor adherence according to web-based CPAP data will receive telephonic interventions from a trained OSA Navigator interfacing with the Project Coordinator. Third, traditional diagnosis of OSA is rendered based on a sleep laboratory assessment, limiting access to many blacks. Fourth, our intervention strategy will be tailored based on information gleaned from focus groups with patients in our previous randomized controlled trial and will draw from family networks, with a focus on input from participants’ partners. Recent evidence shows that partners have either a positive or negative influence on CPAP acceptance [108–111]. Evidence from our previous RCT suggested that partners are instrumental in facilitating adaptation of CPAP therapy in the home environment. Fifth, we will examine both individual- and contextual-level mediators/moderators of intervention effects. Our approach recognizes the interplay of biological and behavioral factors, as well as the influence of contextual factors in determining sleep health behavior in the partner community (Fig. 2) [112].

Our analysis of the BRFSS data revealed several significant social/cultural determinants of sleep deficiency among blacks [113]. They include working more than 40 hours (OR 1.72), caregiving to family/friends (OR 1.23), and lack of emotional support (OR 1.21). Our research among blacks in Brooklyn, NY, also points to significant under-reporting of sleep problems [114, 115], likely due to unique contextual factors [116, 117]. We surmise decisional conflicts affecting adherence to OSA evaluation must be addressed in the context of sociocultural factors hindering optimal sleep [112, 118, 119]. This study will also provide data to examine effects of contextual factors on sleep behavior of blacks. Identifying contextual factors associated with sleep disturbance and specifically OSA is paramount in designing policies to increase health parity in the United States [120, 121].

Success will be determined by achieving the benchmarks of (1) initial screening of 1256 eligible black participants; (2) acquiring data from 50 enrollees per year in each study arm during years 1–4; (3) acquisition of baseline and 6- and 12-month follow-up outcome data by end of year 4; and (4) dissemination in year 5. We propose to achieve a 15% increase in adoption of OSA care, which would have a significant public health impact.

### Limitations and challenges

Our study has several potential design and analytical limitations and challenges. A primary design challenge is to uphold blinding of participant assignment among key personnel. Only the project coordinator and data manager are aware of participant assignment to either the treatment or intervention group. To safeguard against unblinding, we have set up a very strict policy as to who can have access to data (blinded personnel do not have access to data), how project details are communicated in the team where all data are de-identified, and periodic checks to ensure integrity of data will be made by the data manager, who does not attend research project team meetings nor receives project-related email correspondence. A primary analytical challenge is our use of GEE, which is ideal to test our hypotheses and deal with unmeasured dependencies between outcomes. However, GEE requires a large sample size, which the study is powered for, but if we do not meet adequate sample size our power to make meaningful inferences using GEE will be compromised. As an alternative analytical plan, we would use analysis of covariance, which will improve our ability to detect significant effects on our primary and secondary outcomes using a smaller sample size.

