#### Statistical analysis plan

To describe sample characteristics, we will use measures of central tendencies and dispersion for continuous data; frequency distributions will be used for categorical data. We will use χ^2^ tests to compare categorical data and GEE to examine relationships between predictors of adherence to OSA evaluation and/or treatment. The main dependent measure will be adherence to OSA evaluation (yes vs. no) and adherence to CPAP treatment (yes vs. no). Effects of sociodemographic and clinical factors will be adjusted. MANCOVA will be used to assess differences between baseline and 6- and 12-month subjective measures (e.g., self-efficacy, apnea knowledge, functional outcomes in sleep). Structural Equation Modeling will be used to examine the path toward adherence to OSA evaluation and/or CPAP treatment, considering the contributions of candidate factors.

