##### Analysis

We will perform analysis on an intention-to-treat basis. We will assume participants in the intervention arm to have received the full intervention dose and those in the control arm to have received no tailored education. Prior to testing for intervention effects, we will verify comparability of the intervention and control arms with respect to all available sociodemographic data using *t* tests and χ^2^ tests. GEE methods will be used to estimate the odds associated with receipt of OSA evaluation contrasting the two study groups. GEE is preferred over standard logistic regression, as it adjusts for clustering effects. Delays in receipt of endpoint (OSA evaluation or treatment) will be adjusted in the models. Since the type of health educator may influence our findings, we will perform statistical analyses that will detect any potential confounding effect that health educator assignment may have on outcomes. This type of method is distinguishable from a traditional cluster randomized trial as the unit of randomization is at the individual/participant level and not groups of individuals.

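### The ANCOVA fallback for a recruitment shortfall is wrongly credited with a power gain, carries no stated clustering adjustment for yes/no outcomes, and has no defined trigger

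*Protocol article*

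**What the plan says.** All places are in the protocol article.

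- **Limitations and challenges** says that "GEE requires a large sample size, which the study is powered for", and that "if we do not meet adequate sample size our power to make meaningful inferences using GEE will be compromised". It then gives the fallback: "As an alternative analytical plan, we would use analysis of covariance, which will improve our ability to detect significant effects" and, continuing, "on our primary and secondary outcomes using a smaller sample size". It does not say what sample size counts as adequate, and it mentions no cluster term, random effect or robust variance for the ANCOVA.
- **Statistical analysis plan** fixes the outcome type: "The main dependent measure will be adherence to OSA evaluation (yes vs. no) and adherence to CPAP treatment (yes vs. no").
- **Sample size and power analysis** names the primary outcome: "The primary study outcome is receipt of home OSA evaluation after tailored peer-based sleep health education". It allows for an intra-cluster coefficient of 0.014 and states: "A two-tailed test, with 80% power and α = 0.035 comparing adherence rates of 26% with 41% requires 199 participants per group".
- **Analysis, under Primary aim and outcome**, gives the reason for the main method: "GEE is preferred over standard logistic regression, as it adjusts for clustering effects". The effect is to be expressed as odds.

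**The concern.** The fallback is a positive statement about how the primary analysis would be done, and it credits the replacement method with a property. Three things about it look wrong.

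- ANCOVA is a linear model for continuous outcomes. Applied to 0/1 data it draws no more information from them than a logistic model with the same covariates, so a gain from a smaller sample is not to be expected.
- The protocol chooses GEE because of clustering and sizes the trial for it. The fallback names nothing that takes over that role.
- The condition for switching has no number, so nothing in the text stops the primary method from being settled after results are known.

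At stake are the credibility of the primary test if recruitment falls short, and a false reassurance that a shortfall can be repaired by changing the model.

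**Working it through.** **Inputs from the protocol article.** Rates 41% and 26%; two-sided α 0.035; 80% power, and separately more than 85%; 199 per arm; ICC 0.014; DE = 1 + (m − 1)ρ; 35% attrition leaving 258 (129 per arm); educator caseload 3 to 4 at one time; control educators trained differently from intervention educators, so educators are nested in arm. **Not stated:** the total number of participants per educator, m. It is an assumption below.

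**1. The plan's own power figures.**
Power = Φ{[√n·0.15 − z·√(2p̄q̄)] / √(p₁q₁ + p₂q₂)}, with p̄ = 0.335, √(2 × 0.335 × 0.665) = 0.6675, √(0.41 × 0.59 + 0.26 × 0.74) = 0.6590 and z = 2.108 for α 0.035.
- n = 199: (2.116 − 1.407)/0.6590 = 1.075, power 85.9%. This matches the figure above 85%, with no design effect.
- At 80% power the same formula needs 172 per arm. With an assumed m = 12, DE = 1 + 11 × 0.014 = 1.154 and 172 × 1.154 = 198.5, so 199. The 80% statement therefore reproduces with a cluster size near 12, which the article does not state.

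**2. A shortfall lowers power.** Same formula, α 0.035, no design effect: 85.9% at 199 per arm, 67.4% at 129, 55.6% at 100.

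**3. ANCOVA against logistic regression.** With one baseline covariate, no clustering, 129 per arm and two-sided 5%, simulation (2,000 runs) gave 73.0% for ANCOVA and 72.9% for logistic regression.

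**4. With clustering.** Simulated with educators nested in arm, ICC 0.014, m = 12, one covariate, two-sided 5%, 1,300 runs per cell. Each cell shows false-positive rate / power.

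| Per arm | ANCOVA, no educator term | Logistic, no educator term | GEE, uncorrected sandwich | GEE, bias-reduced, t reference |
|---|---|---|---|---|
| 60 | 6.9 / 44.3% | 6.8 / 44.2% | 10.4 / 49.7% | 2.4 / 24.3% |
| 96 | 6.8 / 60.6% | 6.6 / 60.6% | 8.3 / 59.2% | 2.3 / 40.1% |
| 132 | 6.6 / 73.9% | 6.5 / 73.9% | 7.8 / 72.0% | 4.2 / 59.9% |

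The Monte Carlo standard error of a false-positive rate near 6.9% is √(0.069 × 0.931/1300), about 0.7 points, so small differences between cells should not be over-read. ANCOVA and logistic regression are indistinguishable. ANCOVA's extra rejections over bias-reduced GEE reflect ignored between-educator variance and the conservatism of that corrected test, not added information.

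**5. False-positive rate when clustering is ignored.** Rate = 2[1 − Φ(z/√DE)], educators nested in arm, ICC 0.014.

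| m (assumed) | DE | Nominal 5% becomes | Nominal 3.5% becomes |
|---|---|---|---|
| 3 | 1.028 | 5.3% | 3.8% |
| 4 | 1.042 | 5.5% | 3.9% |
| 12 | 1.154 | 6.8% | 5.0% |
| 20 | 1.266 | 8.2% | 6.1% |

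For clusters crossed with arm, such as recruitment sites within which participants are randomized, a simulated unadjusted comparison gave 4.5 to 5.4% against a nominal 5%: no inflation.

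**The case against.** The strongest reply is that the planned method may itself be the worse test. In the simulation, uncorrected sandwich GEE rejects a true null more often than ANCOVA at each size shown (10.4% against 6.9% at 60 per arm), and with m = 20 the gap is 16.0% against 8.6%. A reader might infer that the fallback replaces a valid test with an invalid one. The documents do not support that: they do not say which variance estimator GEE will use, and the authors' worry about GEE in small samples is justified if the clusters are few.

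Other parts of the reply also stand.

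- A reader might infer that the fallback always raises the false-positive rate. It does so only if educators are the clusters and the ANCOVA ignores them. The Analysis section speaks only of clustering in general. Data collection and management plans to look at site effects, and GEE is also to be used at 6 and 12 months, where the clusters could be participants. The Analysis section separately promises to examine educator assignment, and a full analysis plan might add an educator term.
- A reader might infer that a linear model on yes/no data gives an invalid test. At rates of 26 to 41% it tests as well as logistic regression. The mismatch lies in the estimand (a risk difference in place of the planned odds), non-constant variance, and possible fitted values outside 0 to 1. The sample size section itself speaks of a 15-point difference.
- A reader might infer that 35% attrition makes the switch likely. That attrition is already in the plan, and receipt of a home study need not be lost with a missed follow-up visit. Equally, the text does not say that 258 would count as adequate.
- A switch driven by sample size alone does not inflate type I error. The weakness is that the threshold is undefined.

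None of this rescues the statement that ANCOVA will detect effects better in a smaller sample.

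**Conclusion.** The point holds in a limited form. The stated power gain is false: ANCOVA and logistic regression with the same covariate have the same power (about 73% at 129 per arm, two-sided 5%), and power falls with recruitment whichever is used. As written, the fallback also names no replacement for the clustering adjustment on which the sample size and the choice of GEE rest, and its trigger is undefined.

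The effect on false positives is conditional and modest. Over a nominal 5% it is roughly 0.3 to 0.5 points at 3 to 4 participants per educator, about 2 points at 12 and about 3 points at 20. This assumes ICC 0.014, educators nested in arm and no educator term. The cluster sizes are assumptions: the stated caseload applies at any one time, and 12 is only the value that reproduces the 80% power statement. The rise is measured against the nominal level, not against the planned GEE. The small-sample problem is real; ANCOVA is not its remedy.

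**What to change.** In Limitations and challenges, and in the analysis plan if it repeats the text:

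1. Delete the ANCOVA fallback and the claim that it improves detection.
2. Say what the clusters are. At any sample size, keep one prespecified binary-outcome model that accounts for educator clustering, with prespecified covariates. This can be logistic GEE with a small-sample-corrected variance (Mancl-DeRouen or Kauermann-Carroll) and a t reference based on the number of educators, or a mixed logistic model. Choose between them before outcome data are seen.
3. State that power falls if recruitment is short.

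The change is one of wording, and standard software covers it. The statistical cost should be stated openly: intervals widen and, with few educators, apparent power drops noticeably. In the simulation with 12 per educator, bias-reduced GEE had power of 24.3, 40.1 and 59.9% at 60, 96 and 132 per arm, against 49.7, 59.2 and 72.0% for uncorrected GEE. It was also conservative (2.3 to 4.2% against a nominal 5%), which is a reason to compare it with the mixed logistic model before fixing the choice.
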